### Study Setting

This study is conducted at the Medical University of South Carolina (MUSC) in the Kidney Transplant Clinic. MUSC is a tertiary referral academic center in Charleston, SC, and the only transplant center in the state.

### Study Participants

The participants are adult kidney transplant recipients with uncontrolled hypertension who have met the inclusion/exclusion criteria. Potentially eligible study patients were identified through weekly data extractions from the appointment database.

The inclusion criteria for participants were age >18 years (male or female), first- or second-time recipient of a functioning solitary kidney transplantation performed 6 weeks to 60 months earlier, legally competent, assent provided by the transplant physician so that the patient is able to participate, patient prescribed ≥3 medications for immunosuppression and hypertension, electronic pill tray–based medication adherence score <0.85 across a 1-month screening period, uncontrolled systolic hypertension (SBP ≥130 mm Hg) at the screening visit and baseline evaluation (following 1-month medication monitoring period), and 24-hour ambulatory SBP ≥130 mm Hg following the medication monitoring period.

The exclusion criteria were severe cognitive impairment/dementia; inability to self-administer medications, self-measure BP, or use a mobile phone; poor cellular coverage at home; inability to speak, hear, or understand English; history of psychiatric illness or substance abuse; planned pregnancy; and vulnerable populations such as pregnant or nursing women, prisoners, and institutionalized individuals.

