#### Exploratory Outcome Measures

These will include changes in estimated glomerular filtration rate (eGFR) and variability of CNI trough levels (%cv). CNIs have a well-described high inter- and intrapatient variability as well as a narrow therapeutic index. For these reasons, among others, therapeutic drug monitoring of CNI is the standard of care in solid organ transplantation and guides all CNI titrations [67,68]. Changes in the 24-hour ambulatory BP will also be examined.

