### Allocation and Concealment

Subject randomization will be stratified by race and gender and will be conducted by a statistician using a computer-generated random sequence of numbers. Participants who consent to the study and are eligible for randomization at the conclusion of the 1-month medication intake screening period are allocated to either the intervention (SMASK) or SC arm using the computer-generated randomization sequence. Each random sequence is kept concealed in an envelope that is opened by the research coordinator at the time of randomization.

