### Statistical Analyses

#### Primary Outcome Measures

The ITT analysis set will be determined in accordance with the International Conference on Harmonization E9 Guideline “Statistical Principles for Clinical Trials” [70] and will include all randomized subjects. For all subjects included in the ITT analysis set, all available data points will be included in the model. We chose a mixed-effects model approach because this method is a standard method in RCTs and can handle missing data and account for correlated data such as repeated measurements within patients or patients clustered within providers [71-73].

We propose a two-level analysis strategy: Our primary analysis will include the simple mixed-effects model containing the fixed time and intervention group, time, and time-by-intervention as primary independent variables (fixed effects) and MD as a random effect to account for clustering. The main analysis will compare the two intervention groups (SMASK vs SC) at the primary time point outcome at 3 months. We will estimate medication adherence score changes and changes in resting and 24-hour BP for each subject over the trial (preintervention and 1, 3, 6, and 12 months) and the within-subject longitudinal trajectories (eg, slopes) and summarize the mean longitudinal trajectory within each group. Intraclass correlations and variance estimates will be obtained for the efficacy outcomes and covariance structure of the longitudinal scores to determine the sample size (and hence adequate power) for a future effectiveness RCT.

In secondary/exploratory analysis for aim 1 outcomes, the potential influence of *a priori* specified covariates on these models will be explored, including self-determination theory tenants, demographic and clinical characteristics, and comorbidities. In an additional exploratory analysis, effect modifications of covariates will be examined through inclusion of covariate-by-group interaction terms in the multivariable models.

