#### Exploratory Outcomes Measures

In exploratory analyses, change in eGFR, variability of calcineurin trough levels, and 24-hour ambulatory BP will be compared between the two groups using pooled *t* tests (or nonparametric tests, as appropriate). If the end-of study outcomes for eGFR and 24-hour BP are missing, they will be imputed using multiple imputation methods. Further, frequency distributions of adverse events and serious adverse events will be determined, and proportions for the SMASK versus SC groups will be compared using Chi-square analyses.

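### eGFR change and CNI trough %cv are compared by unadjusted t tests although entry spans 6 weeks to 60 months after transplant: no bias, but avoidable loss of precision and exposure to chance imbalance

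*Protocol article*

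**What the plan says.** - **Entry (Study Participants).** Eligible patients have a "functioning solitary kidney transplantation performed 6 weeks to 60 months earlier". The 30-day tray screening precedes randomisation.
- **Allocation (Allocation and Concealment).** "Subject randomization will be stratified by race and gender". The sequence is computer-generated and held in concealed envelopes. Time since transplant is not a stratum.
- **Outcome status (Exploratory Outcome Measures).** Change in eGFR and the %cv of CNI troughs are exploratory. The same paragraph says that "therapeutic drug monitoring of CNI is the standard of care in solid organ transplantation and guides all CNI titrations".
- **Analysis (Statistical Analyses, Exploratory Outcomes Measures).** "change in eGFR, variability of calcineurin trough levels, and 24-hour ambulatory BP will be compared between the two groups using pooled" t tests, with nonparametric tests as the alternative. No covariate is named. Missing end-of-study eGFR is to be multiply imputed.
- **Covariates elsewhere (Statistical Analyses, Primary Outcome Measures).** A covariate exploration is planned, "including self-determination theory tenants, demographic and clinical characteristics, and comorbidities", but for the aim 1 outcomes, which are adherence and blood pressure. The secondary outcomes have adjustment variables of their own. The exploratory outcomes have none.

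**The concern.** The longest permitted time since transplant is about 40 times the shortest (60 months is about 260 weeks; 260/6 is about 43). If eGFR change or trough variability differs between recent and long-standing recipients, time since transplant is a prognostic factor for both outcomes. The plan neither balances it by design nor uses it in the analysis, and it names a test that leaves it in the error term.

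Two things are at stake. The extra between-patient spread widens the standard error of the arm difference. And with 40 per arm, the share of early patients can differ between arms by chance, which moves the estimate in that one trial. The Introduction names %cv, with blood pressure, among the surrogates that the investigators rely on in place of long-term clinical outcomes, so a noisy %cv comparison has some cost even though it is exploratory.

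**Working it through.** **The plan's own figure.** The article gives no power or precision figure for eGFR or %cv. Its only power statement is more than 90% for a 35-point difference in the primary proportions, 40 per arm, two-sided 0.05. The control rate is not stated. Recomputing over all possible control rates gives 89.4% (32.5% vs 67.5%) to 99.3% (0% vs 35%), so the statement reproduces to within rounding. It does not bear on this point.

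**Inputs.** From the article: 40 per arm, random allocation, unadjusted two-sample t test. The two-sided 0.05 level is borrowed from the primary power statement. Assumed, because the article gives no figure: the share of early patients f = 10%, 20% or 30%; the shift in their mean outcome s = 0.5, 1 or 2 within-group SD; a true arm effect of 0.6 SD for the power comparison.

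**Step 1: standard error without adjustment.** With residual SD 1, the outcome variance is 1 + s²f(1−f), so

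SE = √[(2/40)(1 + s²f(1−f))].

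With the factor in the model, SE is about √(2/40) = 0.224. Examples:
- f = 0.2, s = 0.5: √(0.05 × 1.04) = 0.228
- f = 0.2, s = 1: √(0.05 × 1.16) = 0.241
- f = 0.3, s = 2: √(0.05 × 1.84) = 0.303

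The simulated SDs of the arm difference under no effect were 0.227, 0.240 and 0.304, in agreement.

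**Step 2: bias, type I error and power.** 8,000 simulated trials per scenario, pooled t test against a linear model with the early-patient factor:

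| f | s (SD) | Power, unadjusted | Power, adjusted |
|---|---|---|---|
| 10% | 0.5 | 75% | 75% |
| 10% | 1 | 72% | 75% |
| 10% | 2 | 63% | 75% |
| 20% | 0.5 | 74% | 75% |
| 20% | 1 | 69% | 75% |
| 20% | 2 | 55% | 75% |
| 30% | 0.5 | 73% | 74% |
| 30% | 1 | 68% | 76% |
| 30% | 2 | 50% | 75% |

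Under no true effect, the mean arm difference was within 0.005 SD of zero. The rejection rate was 4.6-5.1% unadjusted and 4.4-5.3% adjusted. The unadjusted test is therefore valid, and only precision changes.

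**Step 3: chance imbalance.** The SD of the difference in early share between arms is √[2f(1−f)/40], which is 0.067, 0.089 and 0.102 for f = 10%, 20% and 30%. An imbalance of 15 points or more (6 of 40 patients) occurred in about 4%, 12-13% and 17-18% of simulated trials. A 15-point imbalance moves the unadjusted estimate by 0.15 × s: 0.075, 0.15 or 0.30 SD for s = 0.5, 1 or 2. The last is half of a 0.6 SD effect.

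**Limits.** The simulation uses one correctly specified binary factor and simple 40:40 allocation. If the modelled form of time since transplant (for example log months) fits less well, the gain is smaller.

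**The case against.** **Exploratory outcomes, condensed article.** These outcomes carry no power claim or decision rule, and the limitations paragraph already concedes that 12 months is too short to show improved graft function. Details of exploratory tests are often left to the analysis plan. This limits the weight of the point. It does not remove it, because the article does not stay silent: it names the test, and a better one is available.

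**eGFR is already analysed as change.** True, and this handles baseline in part, with its slope fixed at 1. Putting baseline in the model estimates the slope instead. It does nothing for time since transplant.

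**Stronger readings a reader might infer.**

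1. *Early dose titration and graft recovery will be mistaken for adherence effects.* This does not follow. Time since transplant precedes a concealed random allocation and is balanced in expectation, and Step 2 shows no systematic arm difference.

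2. *The %cv is defined on raw troughs, so every prescribed dose change counts as variability.* The article gives no formula, sampling window or handling of dose changes, so this reads a definition into silence. Suppose, purely as an assumption, that exposure falls linearly by a fraction k. The drift then contributes a %cv of (k/√12)/(1−k/2), which is 6.4%, 10.2% and 19.2% for k = 0.2, 0.3 and 0.5. Combined in quadrature, an underlying 20% becomes 21.0%, 22.4% and 27.8%. That is inflation within a patient, in either arm. It is not a difference between arms.

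3. *Better adherence in SMASK raises levels, prompts dose changes and so raises its %cv.* This route is post-randomisation and randomisation would not cure it. But the article gives nothing on its frequency or size, it does not depend on the entry window, and adjusting for time since transplant would not address it. What stands is that, since troughs guide titration, %cv may reflect prescribing as well as intake. That justifies a supportive analysis, not a claim of error.

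**Conclusion.** The stated analysis of eGFR change and CNI trough %cv is valid but inefficient. It leaves out a potentially prognostic factor known from eligibility and, for eGFR, a baseline value that Table 1 schedules, and it leaves a single trial of 40 per arm open to chance imbalance in early-transplant patients. Over the assumed range (early share 10-30%, true effect 0.6 SD), the loss runs from about 1 point of power or less at a 0.5 SD shift, through 3-8 points at 1 SD, to 12-25 points at 2 SD. The article does not say where in this range the trial lies. The documents do not support a charge of bias, of a faulty %cv definition, or of any effect on the primary or secondary outcomes. This is a minor point: an improvement to make because it is nearly free.

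**What to change.** In Statistical Analyses, Exploratory Outcomes Measures, replace the pooled t tests for these two outcomes with a linear model containing:
- treatment group;
- time since transplant at randomisation, for example log months, with the form fixed in advance;
- the stratification factors, race and gender;
- for eGFR, the baseline value.

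Keep the unadjusted t test (or its nonparametric alternative) as a sensitivity analysis. For eGFR, fit the model within the multiple imputation already planned and include the same covariates in the imputation model.

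Optionally, add a %cv of dose-normalised troughs (trough divided by the prescribed daily dose at the time) as a supportive sensitivity analysis, since troughs guide titration.

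**Cost.** The main change is a matter of wording, with no new patient data: time since transplant is established at eligibility, and eGFR is scheduled at baseline. Enrolment is complete, so the strata cannot change, but the model can still be fixed before outcomes are compared by arm. It spends a few degrees of freedom out of 80 patients. The dose-normalised %cv is the only part with a real burden: prescribed-dose history would have to be extracted in both arms.

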### Prototype of the Mobile Health Smartphone Medication Adherence Saves Kidneys System

The SMASK mHealth system characterized in Figure 2 consists of a wireless global system for mobile communication electronic medication tray (Vaica, Tel Aviv, Israel), a wireless validated Bluetooth low energy–enabled BP monitor (UA-767 Plus BT device [46]), and a smartphone (Android running Lollipop or newer operating system or iPhone 4 or newer). The medication tray plugs into an ordinary 110 V outlet, has 28 compartments (up to 4 doses per day for 7 days), time stamps compartment use, and is capable of providing reminder signals. At the prescribed dosing day and time, a blinking blue light is activated. If, after 30 minutes, the compartment lid has not been opened and closed, a loud intermittent chime automatically activates for 30 minutes. If, at the end of those 30 minutes, the compartment lid still has not been opened, an automated reminder phone call or SMS is delivered to the subject’s mobile phone. Microelectronic circuitry in each compartment on the tray date and time stamps the opening of the compartment lid. These signals are relayed via an internal modem to the Viaca server for processing. Data will then be sent directly to a HIPAA (Health Insurance Portability and Accountability Act of 1996)-compliant relational database housed at MUSC. Personalized motivational and positive reinforcement SMS messages will be automatically delivered initially based on the previous day’s calculated medication adherence. After 2 consecutive weeks of a calculated adherence score of 1.0, message delivery will be tapered from daily to several times per week on a 3-day average variable interval schedule. The schedule will revert to daily delivery when and if a subject’s calculated weekly adherence score is <0.9. The library of motivational/social reinforcement SMS messages was developed by enhancing the library of messages used in the earlier mHealth medication adherence studies [25,26]. This step was guided by underlying tenants of competency (akin to self-efficacy) and autonomous motivation from the self-determination theory [47,48], tailored to the subject based on their responses to a questionnaire designed to identify underlying motivating themes for consistently engaging in the medical regimen.

Participants will be sent SMS messages every 3 days as a reminder to measure their BP with the Bluetooth-enabled A&D UA-767 Plus BP monitor (A&D Medical, San Jose, CA). They will be instructed to measure their BP in the morning and evening every third day by using our resting BP protocol (described under Clinic Resting Blood Pressure). They will also receive a tailored positive reinforcement SMS message the day after successful completion of their BP measurements. An app will be installed on their smartphone, which will securely receive and transmit the BP data to the MUSC-housed server. The app will also provide text instructions throughout the BP protocol and a video clip module demonstrating use of the app and the BP monitor.

A weekly SMASK dashboard summary report, tailored to the treating physician’s preferences, will be delivered via email (Figure 3). The report will summarize each subject’s medication adherence and adherence to the BP self-monitoring schedule for the prior 2 weeks. Color coding will be used to indicate where the subject lies relative to the desired goals (ie, SBP <130 mm Hg and adherence score >0.90). In addition, a breakdown of the BP readings obtained over the 2 weeks will be provided with systolic and diastolic pressures. The treating physician will make adjustments to the medical regimen, as indicated and guided by the KDIGO guidelines [49]. The physician will notify the study coordinator of the changes via email. Any medication changes made by the treating physician will be mirrored in the programming of the medication tray after the study coordinator confirms with the patient that the changes have been enacted. The research manager and staff will be contacted via email, and the SMASK participants will be contacted via their preferred mode (SMS, email, or phone) when they fail to measure BP or when the measured BP is outside of the threshold ranges established by the treating physician, or they will be contacted via an SMS text when the SimpleMed+ tray identifies lack of medication adherence.

**Figure 2 figure2:**
[figure not shown]
“Smartphone Medication Adherence Saves Kidneys” schematic.

**Figure 3 figure3:**
[figure not shown]
Example of a “Smartphone Medication Adherence Saves Kidneys” participant’s weekly summary report to the provider. AVG RDG: average reading, SBP: systolic blood pressure; BP: blood pressure; MRN: medical record number.

### Calculation of Adherence Score

A detailed description of the medication adherence score calculation by Russell et al is available elsewhere [50]. We will employ a modification of the algorithm to allow for dosing schedules other than the twice daily schedule. Our subjects will be instructed that to be considered fully adherent, their medications have to be taken within a 3-hour window of the prescribed dosing time. A dose taken within the 3-hour window will be assigned a full score for that dosing time, a dose taken outside the 3-hour window but within a 6-hour window will be assigned a half score for that dosing time, and a missed dose will be assigned a score of 0. Each subject will be assigned a score from 0.0 to 1.0 for each day. The scores for each subject will be averaged over each week.

### Identification of Medication Nonadherent Patients with Uncontrolled Hypertension

Patients who meet the initial eligibility criteria, including a resting BP evaluation (SBP ≥130 mm Hg), and provide informed consent will be enrolled in a 30-day screening period using the SimpleMed+ with its reminder functions disabled. Subjects will be given a demonstration of how to properly use the medication tray and will be required to demonstrate successful use of the tray before completion of the visit. They will receive written and oral instructions explaining that to be considered fully adherent, they must take their medications within 90 minutes of the prescribed dosing time. After confirming successful connection with the server, the tray will be programmed by the study manager to accurately reflect the subjects’ medication dosing schedule. At the conclusion of the 1-month screening period, our modification [25] of the adherence equation by Russell et al will be used to calculate a medication adherence score for each subject. Only subjects with a cumulative adherence score <0.85 across the 1-month screening period will be eligible for randomization to either the mHealth intervention group or the attention control SC group.

### Attention Control Standard Care Group

The enhanced attention control SC group will receive SC at the MUSC Kidney Transplant clinic. SC includes clinic visits as deemed appropriate, education on all matters related to posttransplantation medical care, and 24-hour phone availability of transplant coordinators. Participants randomized to the SC group will continue to use their SimpleMed+ medication tray, with its reminder functions still disabled, for an additional 6 months. To control for attention exposure, the subjects in the SC group will receive SMS messages on health-related topics excluding medication adherence. These messages include healthy lifestyle tips related to physical activity, dietary intake, nonexposure to first- or second-hand smoke, and limited alcohol intake. The SMS messages will be delivered every 3 days to approximate the schedule of the mHealth intervention group. SMS messages will include links to video or PDF content that require 3-5 minutes to review.

### Mobile Health Intervention

The participants randomized to the intervention arm will receive the SMASK mHealth system, described in detail above, for the 6-month active trial. Subjects will be provided and instructed on use of the previously validated A&D BP device, and the SMASK app will be installed on their smartphone. The escalating reminder functions of the SimpleMed+ will be enabled. The SMASK subjects will again receive written and oral instructions on adherence criteria (ie, all medications are to be taken within a 180-min window centered on the dosing time; BP is to be measured every 3 days).

SMASK subjects will complete a questionnaire on beliefs, values, and life goals with the responses used in a tree-structured algorithm to generate tailored motivational and positive reinforcement messages that are delivered to promote self-efficacy for medication adherence and autonomous regulation for sustained behavior change.

A technical support phone number will be provided in several forms (paper copy, refrigerator magnet, and SMASK app) for assistance. At the conclusion of the study, subjects will return the SimpleMed+, A&D BP monitor, and smartphone (if one was borrowed) and complete a brief questionnaire assessing their opinions of the mHealth system.

### Active Trial Evaluations and Follow-Up Phase

All subjects will be followed up for an additional 6 months following the 6-month active trial. Patients will continue to attend the clinic at a frequency determined by the provider. At 1, 3, 6, and 12 months after randomization into the SMASK or SC group, subjects will be assessed on medication adherence using medication possession ratio checks, clinic resting BPs, and completion of a brief set of questionnaires including measures to assess self-determination theory tenants of autonomous self-regulation and self-efficacy (Table 1). Providers are assessed on adherence to BP management protocols and goals. The timeliness and appropriateness of medication changes will be evaluated according to KDIGO guidelines across both groups at the conclusion of the study.

**Table 1 table1:** List of measures and evaluation time points.

Outcome variables		Measurements/instruments used	Screening	Baseline	1 month	3 months	6 months	12 months
